### Data Management and Monitoring

Participant confidentiality will be maintained using unique identifier codes, with de-identified data entered directly into the secure REDCap (Research Electronic Data Capture) database [30]. Electronic and hard-copy data will be stored on password-protected university servers and in locked cabinets, respectively, and retained for 7 years after the study. As this noninterventional study presents no anticipated risks, a data monitoring committee is not required, and monitoring will be performed by the principal investigator and the research team.

### Sample Size Calculation

The minimum required sample size is calculated using the single-population proportion formula [31], based on T2DM with MetS prevalence of approximately 11.2% in Hong Kong [32]. With a 95% confidence level, a precision of SD 3%, and an assumed nonresponse rate of 10%, the study aims to recruit 470 participants.

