## Introduction

Diabetes mellitus (DM) presents a critical global health challenge, with its prevalence escalating rapidly. As of 2021, approximately 537 million adults were affected, with projections estimating a rise to 783 million by 2045 without effective preventive measures [1]. Type 2 diabetes mellitus (T2DM) constitutes over 90% of these cases, underscoring its significance in the diabetes epidemic [2]. In Hong Kong, T2DM impacts nearly 10% of the adult population, mirroring global trends [3]. Adults with DM exhibit a 2-4 times higher risk of cardiovascular complications compared to adults with no DM [4]. Alarmingly, 65%-85% of patients with T2DM meet the diagnostic criteria for metabolic syndrome (MetS) [5,6], characterized by abdominal obesity, hypertension, dysglycemia, and dyslipidemia [7,8]. MetS impacts 20%-25% of the global population [9] and serves as an independent predictor of mortality among individuals with diabetes. This coexistence exacerbates metabolic abnormalities and increases cardiovascular risk, underscoring the imperative for early diagnosis and intervention to enhance management and prevent chronic complications [10,11].

Although conventional pharmacotherapy targets individual MetS components (eg, hypoglycemics, statins, and antihypertensives), emerging evidence supports Traditional Chinese Medicine (TCM) as a complementary approach. Clinical trials demonstrate that integrating TCM with Western regimens yields superior improvements in anthropometrics (eg, waist/hip circumference), glycemic control (glucose, glycosylated hemoglobin), insulin resistance index, and triglycerides, with minimal adverse reactions [12]. This aligns with a systematic review of 16 randomized controlled trials, where TCM significantly enhanced weight management and metabolic regulation [13]. Mechanistically, TCM compounds modulate lipid metabolism, vascular endothelial function, and insulin sensitivity via the phosphatidylinositol 3-kinase/protein kinase B signaling pathway, peroxisome proliferator-activated receptor pathway, and AMP-activated protein kinase pathway, offering multitargeted correction of metabolic dysregulation [14]. Together, clinical and pharmacological evidence supports TCM’s role in addressing the complex interplay of T2DM and MetS.

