### Study Procedure and Population

We aim to recruit a cohort of 470 adult participants (age ≥18 years) diagnosed with both T2DM and MetS [19]. The inclusion and exclusion criteria are detailed in Textbox 1. Following screening, enrolled participants will proceed to complete the study assessments. Participants who complete all study procedures will receive a transportation allowance of HK$100.

Inclusion and exclusion criteria for participation.

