### Study Outcomes

The primary outcome will be the TCM syndrome differentiation in patients with T2DM and MetS, as assessed by the Syndrome Differentiation Questionnaire for T2DM and MetS (SDQTM). SDQTM is developed according to the Guideline for the Integrated Diagnosis and Treatment of Metabolic Syndrome [20], Guideline for the Integrated Diagnosis and Treatment of T2DM [21], and Guiding Principles for Clinical Research of New Chinese Medicine [22]. It includes 69 items (Textbox 2) that capture disease nature (eg, wind, dryness, yang deficiency) and location (eg, heart, kidney) [23]. Each item is a closed-ended question featuring a ranked scale with descriptors for symptom severity and frequency. Registered Chinese medicine practitioners will administer SDQTM in a face-to-face consultation integrating the 4 TCM diagnostic methods.

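### The 470 target is sized on the population prevalence of T2DM with MetS, which an all-case study does not estimate, so its 3% precision does not apply to the primary outcome

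*Protocol article*

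**What the plan says.** The Sample Size Calculation section names its method: "The minimum required sample size is calculated using the single-population proportion formula". The proportion entered is the population prevalence of the comorbidity: "based on T2DM with MetS prevalence of approximately 11.2% in Hong Kong". The remaining inputs and the result follow: "With a 95% confidence level, a precision of SD 3%, and an assumed nonresponse rate of 10%, the study aims to recruit 470 participants".

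Two other sections bear on whether that proportion fits. Under Study Procedure and Population the article states: "We aim to recruit a cohort of 470 adult participants (age ≥18 years) diagnosed with both T2DM and MetS". The inclusion criteria in Textbox 1 likewise require both diagnoses. Under Study Outcomes: "The primary outcome will be the TCM syndrome differentiation in patients with T2DM and MetS". The Introduction gives the same aim, to identify which syndromes are common among people with both conditions. The Statistical Analysis section identifies the syndrome patterns by latent class analysis.

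**The concern.** The single-proportion formula gives the number of people needed to estimate a named proportion to within a chosen margin. Here the named proportion is how common T2DM with MetS is in Hong Kong. Estimating that would take a sample from the general population, with and without the conditions. This study enrols only people who have both, so the proportion is 100% by design.

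What the study does estimate is how the syndromes are distributed among cases. No expected value for any syndrome proportion is given, and nothing links 11.2% to one. The only reason stated for 470 therefore concerns a quantity outside the study, and the 3% attached to it says nothing direct about the primary outcome. At stake is how precise the main results are understood to be, especially for the common syndromes the study sets out to identify.

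The precision is also labelled as an SD. An SD is not a margin of error, and the label does not match what was computed.

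**Working it through.** **Inputs (Sample Size Calculation section).** p = 0.112; 95% confidence, so z = 1.96; d = 0.03; nonresponse 10%; stated result 470.

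**Step 1. Reproduce the plan's figure.** n = z² p(1 − p) / d²

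- 1.96² × 0.112 × 0.888 / 0.03² = 3.8416 × 0.099456 / 0.0009 = 424.5, rounded up to 425.
- Nonresponse by division: 425 / 0.9 = 472.2, rounded up to 473.
- Nonresponse by multiplication: 425 × 1.1 = 467.5, rounded up to 468.

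The stated 470 lies between these, so the calculation is reproduced.

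**Step 2. What the 3% is.** If 3% were a standard error, n = 0.112 × 0.888 / 0.0009 = 110.5, or 111. That is nowhere near 425. Only a 95% CI half-width of 3 percentage points reproduces 470, so the SD label is a misprint.

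**Step 3. Precision for a proportion the study can estimate.** The article gives no expected syndrome prevalence, so the values of p below are assumed. Half-width = 1.96 × √(p(1 − p)/N), for a directly observed yes/no proportion. N = 423 is 470 less 10% (470 × 0.9). N = 450 reflects the Results section, which reports more than 450 with completed data collection by October 2025. N = 470 is the full target.

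| Assumed proportion | N = 423 | N = 450 | N = 470 |
|---|---|---|---|
| 10% | 2.9 | 2.8 | 2.7 |
| 20% | 3.8 | 3.7 | 3.6 |
| 30% | 4.4 | 4.2 | 4.1 |
| 50% | 4.8 | 4.6 | 4.5 |

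(Percentage points. Values for 70%, 80% and 90% mirror those for 30%, 20% and 10%.)

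**Step 4. Where 3 points is met.** Solve p(1 − p) = N × 0.03² / 1.96².

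- N = 423: p(1 − p) = 0.3807 / 3.8416 = 0.0991, so p is at most about 11.2% or at least about 88.8%.
- N = 470: p(1 − p) = 0.423 / 3.8416 = 0.1101, so p is at most about 12.6% or at least about 87.4%.

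**Step 5. Limit of these figures.** They treat each syndrome as directly observed. Shares estimated by latent class analysis also carry uncertainty about which class a participant belongs to, so the Step 3 values are not an upper bound for them.

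**The case against.** Several points on the other side stand.

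- **No explicit claim about syndromes.** A reader might infer that the plan promises syndrome prevalences accurate to within 3 points. It does not: the 3% is attached only to the 11.2% calculation. What the text supports is that the justification does not bear on the primary outcome.
- **The arithmetic is sound.** The error is in the choice of parameter.
- **The loss is moderate.** With data collection complete for more than 450, the worst case is about 4.6 points, and 4.5 at 470. Proportions near 11% or lower keep 3 points. Whether common syndromes miss it depends on prevalences the article does not give.
- **A binomial bound need not cover latent classes.** A restatement promising at most 4.8 points for any syndrome would itself claim too much. It must be confined to directly observed proportions.

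A further reading is that 11.2% contradicts the Introduction, which says "In Hong Kong, T2DM impacts nearly 10% of the adult population" and "65%-85% of patients with T2DM meet the diagnostic criteria for metabolic syndrome", since a subset cannot be more common than the whole. The documents do not establish this. The three figures come from separately cited sources whose populations, years and definitions are not shown, and the 65%-85% figure is not presented as specific to Hong Kong. It is a secondary tension, and it becomes moot once the 11.2% rationale is removed.

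None of this rescues the choice of parameter. Nor does condensation into a journal article: the formula, its input, the precision and the result are all printed, and a fuller document could not make the population prevalence something this design estimates.

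**Conclusion.** The point holds as a mismatch between the sample-size parameter and the study's primary outcome. The 470 is correctly calculated for a proportion that the study fixes at 100% by eligibility. The stated 3% is a 95% half-width misprinted as an SD, and it does not carry over to the syndrome distribution.

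For a directly observed proportion with 423 evaluable, the half-width reaches 4.8 points at 50%, which is 1.8 points wider than the printed 3. Three points is met only at the extremes, at or below about 11% or at or above about 89%. These figures rest on assumed prevalences, the usual normal-approximation interval and a directly observed yes/no outcome.

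A reader might go further and infer that 470 is too small. The documents do not support that: they set no precision target for syndrome proportions, and a margin below 5 points may well be adequate for description. The fault lies in the justification, which should be corrected before results are reported.

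**What to change.** Keep 470 and rewrite the Sample Size Calculation section.

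1. Delete the rationale based on the 11.2% population prevalence.
2. Replace the SD wording with a 95% CI half-width in percentage points.
3. State the precision for what is estimated, for example: With about 423 to 470 evaluable participants, a directly observed proportion (a questionnaire item or an assigned syndrome) is estimated with a 95% CI half-width of at most about 4.8 percentage points. The half-width is 3 points or less only for proportions at or below about 11%, or at or above about 89%, if 423 are evaluable.
4. Add that shares from the latent class analysis carry additional classification uncertainty and may be less precise.
5. Report each syndrome proportion or class share with its own confidence interval.

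The cost is wording. The stated precision becomes less favourable, from 3 to as much as about 4.8 points. No further participants are needed and the planned analysis methods do not change.

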### Statistical Analysis

Statistical analysis will be performed using SPSS (version 29.0; IBM Corp), Python (version 3.13.9), and R (version 4.5.2; R Foundation for Statistical Computing) software. Missing values will be imputed by multiple imputation using the chained equation method. Quantitative data will be summarized as mean (SD) if normally distributed or as median and interquartile range otherwise. Latent class analysis will be used to identify the TCM syndrome patterns. Factor analysis will be used to reduce the dimensions of TCM syndrome elements and explore their underlying structure. Data suitability will be evaluated using the Kaiser-Meyer-Olkin measure and Bartlett's test of sphericity. Principal component analysis with varimax rotation will be employed to extract the common factors. Based on the factor analysis results, hierarchical cluster analysis will be performed to classify TCM syndrome elements. Cluster boundaries will be determined by identifying large distances between successive fusion levels in the dendrogram. The adjusted Rand index will be used for measuring the agreement between classifications.

For the comparison of quantitative data, one-way analysis of variance will be used if the assumptions of normality and homogeneity of variance are met. Otherwise, the Kruskal-Wallis test will be used. Categorical data will be expressed as numbers and percentages, and comparisons will be conducted using the chi-square test or Fisher exact test, as appropriate. Spearman correlation analysis will be employed to evaluate correlations between continuous variables, and Kendall’s tau-b analysis will be used for ordinal variables. Logistic regression will be performed to examine the relationship between syndrome differentiation and MetS components. A 2-sided value of *P*<.05 will be considered statistically significant.

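### Latent class analysis alone cannot tell distinct TCM syndromes from bands of overall symptom severity, and the plan states no comparison that could

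*Protocol article*

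**What the plan says.** Study Outcomes: "The primary outcome will be the TCM syndrome differentiation in patients with T2DM and MetS", assessed by the SDQTM. Of that questionnaire it says "It includes 69 items" and "Each item is a closed-ended question featuring a ranked scale with descriptors for symptom severity and frequency". The item list (Textbox 2) contains items that repeat or combine each other's content. Examples are wiry, slippery, and wiry-and-slippery pulse; rapid, and thready-and-rapid pulse; two dry-mouth items; and two edema items.

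Statistical Analysis: "Latent class analysis will be used to identify the TCM syndrome patterns". Principal components with varimax rotation and hierarchical clustering are then applied to syndrome elements, and "The adjusted Rand index will be used for measuring the agreement between classifications". The article states no comparison of the classes with a continuous severity model.

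**The concern.** Under local independence, the one-class model says that no two items are associated. Any sufficiently strong association between items therefore counts in favour of a further class, whatever its source. Two sources other than distinct syndromes are plausible here: general symptom burden, because items are graded for severity and frequency, and repeated item content.

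If burden dominates, the classes are ordered bands (milder, more severe) and not different patterns. Such bands could still be associated with metabolic markers, cardiovascular risk and quality of life. They could then be reported as the syndrome-specific relationships expected under Anticipated Principal Findings and used for the personalized treatment discussed under Implications for Practice or Research.

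**Working it through.** **The plan's own figure.** Inputs from Sample Size Calculation: prevalence 11.2%, precision 3%, 95% confidence, 10% nonresponse. 1.96² × 0.112 × 0.888 / 0.03² = 424.5, so 425. Dividing 424.5 by 0.9 gives 471.7; 425 × 1.10 gives 467.5, so 468. The stated 470 is reproduced. It does not bear on this point except to set N for the simulations.

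**What a further class has to earn.** BIC = −2 log L + p ln N, with p = (K − 1) + K × J × (L − 1) for K classes, J items and L levels. With J = 69 and L = 2, p is 69 for one class and 139 for two. The second class must therefore reduce −2 log L by more than 70 × ln 470 = 70 × 6.153 = 430.7. With L = 4 it must reduce it by more than 208 × 6.153 = 1,279.8. Weak association does not clear this bar, so the size of the burden factor matters.

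**Simulation, no true classes.** N = 470 and 69 items. Assumed, because the article does not give them: 2 or 4 levels, a symptom present in 20% to 60% of patients, and the factor strengths and correlations below. The share of variance is the squared loading, so 10% is a loading of 0.32.

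*One severity factor on all 69 items, 12 data sets per cell, 1 to 6 classes tried:*

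| Variance from severity | Classes by BIC, 2 levels | Classes by BIC, 4 levels |
|---|---|---|
| 0% | 1 in 12/12 | 1 in 12/12 |
| 10% | 2 in 12/12 | 2 in 12/12 |
| 20% | 3 in 12/12 | 2 in 12/12 |
| 30% | 3 or 4 in 12/12 | 2 or 3 in 12/12 |

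Mean entropy in the cells with severity was 0.82 to 0.97, so the spurious classes look well separated.

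*Severity on symptom items only.* A burden factor may not reach the 8 tongue and 9 pulse items, which leaves 69 − 17 = 52. With yes/no items, BIC chose two classes in 12/12 at loadings of 0.3 or more on 52 items, and in 12/12 at 0.4 on 30 items. It did so in only 0 to 1 of 12 at 0.2 to 0.25 on 52 items, or at 0.3 on 30. A rerun with frequencies of 20% to 60% agreed at 0.2 (0 of 20) and 0.3 (20 of 20) on 52 items, but gave two classes in 14 of 20 at 0.25. A loading of 0.25 is best read as the border, where the result turns on the assumed frequencies.

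*Wording overlap only (correlated errors within overlapping item sets):*

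| Residual correlation | More than 1 class by BIC, 2 levels | More than 1 class by BIC, 4 levels |
|---|---|---|
| 0.5 | 0/12 | 0/12 |
| 0.8 | 7/12 | 0/12 |

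A separate yes/no simulation of 40 data sets gave 30% with overlap in tongue and pulse items, and 48% when symptom items were added. AIC chose more than one class in 47 of the 48 data sets in the table. That is weak evidence, since AIC also did so in 7 of 12 data sets with fully independent yes/no items. Adding overlap of 0.5 to a 20% severity factor left the BIC choice unchanged (3 classes with 2 levels, 2 with 4 levels).

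**Does a one-factor comparison discriminate?** With yes/no items the one-factor model has 2 × 69 = 138 parameters against 139 for two classes, so the two penalties are nearly equal. With severity only (loading 0.35, 20 data sets), BIC preferred two classes to one in 20/20, but the one-factor model beat every class model in 20/20 and the class profiles were parallel. With three genuine crossing classes, BIC chose three in 20/20 and the one-factor model never won.

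**The case against.** - **This is detail for an analysis plan that is not shown.** That holds for the class-number criterion, the coding of items and the residual checks; their absence is no finding. The inferential gap remains: the method named for the primary outcome cannot by itself support a claim of distinct patterns.
- **A ranked format does not create a common factor.** Correct. The article says that each item has a ranked scale, not that all share one. The list also contains opposites, such as pale and red tongue or loose and hard stools. The factor's strength is an assumption. This is why the result is given as a threshold, and why the case without tongue and pulse items matters.
- **The inputs may not be the 69 items.** The article does not say whether items or derived elements enter the model. If elements do, the simulated frequencies do not carry over, though combining items would not remove a burden common to them.
- **Other methods are planned.** True, but factor analysis and clustering use the same correlated content, the clustering is of elements and not of patients, and the adjusted Rand index measures agreement. None compares syndromes with severity bands.

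A reader might infer that any correlation between items produces false syndromes, or that overlapping wording breaks the model by construction. The results do not support this: BIC withstood moderate overlap throughout, and strong overlap with four-level items. Nor are scoring rules for compound signs given. If practitioners record only the best-fitting sign, the dependence would be negative rather than duplicated. A reader might also infer that the classes feed every later comparison and regression; the article does not name the grouping variable.

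**Conclusion.** The point holds as a limit on what the primary analysis can show. With an assumed general burden loading of about 0.3 or more across most symptom items, BIC reports two or more classes in essentially every data set of 470 that contains none. At 0.2 it almost never does, and around 0.25 the outcome depends on symptom frequencies. Wording overlap is secondary. The figures rest on the assumed loadings, frequencies and response levels, and on BIC as the selection rule. They do not show that this study's data contain such a factor, or how far real syndromes would be distorted. The point should be settled before analysis.

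**What to change.** In Statistical Analysis, add three statements:

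1. A one-dimension severity (latent trait) model will be fitted to the same indicators as the latent class model.
2. Distinct syndrome classes will be claimed only if the class model has the better BIC and the class profiles cross. If profiles run parallel, or the severity model fits better, the classes will be reported as severity levels.
3. Bivariate residuals will be checked. As a sensitivity analysis, residual associations will be freed for item pairs with overlapping wording, or those items merged.

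A full recoding of the tongue and pulse items is not needed, and a compound sign graded on one scale does not split uniquely into features. The questionnaire stays as it is, which matters because the Results section reports more than 450 participants with completed data collection. The cost is one additional model, a few sentences, and possibly fewer classes that can be called syndromes.

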**Methods:**

This cross-sectional study will enroll a cohort of 470 participants diagnosed with T2DM and MetS. All participants will undergo comprehensive assessments, including the Syndrome Differentiation Questionnaire for T2DM and MetS, demographic and anthropometric measurements, biochemical profiling (eg, fasting glucose, glycosylated hemoglobin, and lipid panel), dietary measurement (Food Frequency Questionnaire), physical activity measurement (International Physical Activity Questionnaire Short Form), sleep quality evaluation (Pittsburgh Sleep Quality Index), quality-of-life assessment (Audit of Diabetes-Dependent Quality of Life), stroke risk estimation (Framingham Stroke Risk Score), and retinal imaging. Latent class analysis will be used to identify the TCM syndrome patterns. Factor analysis will be employed to identify core TCM syndrome factors. Hierarchical cluster analysis will be performed to classify TCM syndrome elements, and logistic regression will examine associations between syndrome differentiation, metabolic parameters, lifestyle factors, and disease progression.

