Items of The Syndrome Differentiation Questionnaire for Type 2 Diabetes Mellitus and Metabolic Syndrome (SDQTM).Fatigue and weaknessShort of breath and want of speechSpontaneous sweatingPale or sallow yellow complexionPale lips and fingernailsDizzinessDry throat and mouthSensation of heat in the palms, soles, and chestHot flashes or night sweatsAversion to cold and cold limbsPuffy face and edema of the feetWeak coughSusceptibility to common coldsReduced food intake and poor appetiteAbdominal distension after eatingLower back and knee weaknessTinnitus and deafnessLoose teeth and hair lossDecreased libidoPalpitationsInsomnia and profuse dreamingForgetfulnessBlurred visionLusterless nailsNumbness in the hands and feetDry eyesIrritability or depression with frequent sighingCold pain in the abdomenThirst with desire for cold drinksExcessive eating and easy hungerFullness in chest and hypochondriumDistending pain in the abdomenGeneralized edemaHeavy sensation in the limbsDry mouth and bitter tasteDusky or dull dark complexionPurplish dark lipsSquamous and dry skinFixed painPetechiae on the skinNauseaVomitingItching skinSticky, greasy sensation in the mouthDark yellow or reddish urineFrequent urination in large volumeFrequent nocturiaScanty urineDry hard stoolsLoose stoolsAtonic constipationDark urine and constipationEnlarged tongue with teeth marksPale tongueRed tongue with scant coatingPale, enlarged tongue with a moist coatingRed tongue with yellow coatingYellow and greasy tongue coatingPurplish dark tongue, sublingual vein engorgementSlippery and greasy tongue coatingWeak and forceless pulseThready and weak pulseThready and rapid pulseDeep and slow pulseRapid pulseWiry pulseWiry and slippery pulseChoppy or intermittent pulseSlippery pulse

The secondary outcomes include demographic and anthropometric measurements, blood pressure, fasting glucose, glycosylated hemoglobin, lipid panel (total cholesterol, triglycerides, high-density lipoprotein, low-density lipoprotein), International Physical Activity Questionnaire-Short Form, Food Frequency Questionnaire, Pittsburgh Sleep Quality Index, Audit of Diabetes-Dependent Quality of Life, Framingham Stroke Risk Score (FSRS), retinal imaging, and concurrent medications.

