### Strengths and Limitations

This study has several strengths, including its design as the first large-scale cross-sectional investigation systematically characterizing TCM syndromes in individuals with T2DM and MetS. This research innovatively integrates clinical indicators such as biochemical profiling and retinal imaging with TCM syndrome differentiation while also incorporating evaluations of health behaviors and quality of life. However, several limitations should be acknowledged. The cross-sectional design inherently prevents establishing causal relationships, and reliance on self-reported data may introduce recall bias. Additionally, potential confounding factors could affect result interpretation, and the generalizability of the findings beyond the studied population requires further validation.

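### The named group comparisons cannot adjust and no model names a covariate, so syndrome differences may partly reflect age, sex or treatment

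*Protocol article*

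**What the plan says.** The Statistical Analysis section allots comparisons by data type. For continuous measures it says that "one-way analysis of variance will be used if the assumptions of normality and homogeneity of variance are met". The fallback when those assumptions fail is Kruskal-Wallis. For categorical data, "comparisons will be conducted using the chi-square test or Fisher exact test, as appropriate". Spearman and Kendall tau-b coefficients cover correlations. The section does not name the groups being compared. Given the study's aim, they are presumably the syndrome patterns.

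One model could carry covariates. The same section says: "Logistic regression will be performed to examine the relationship between syndrome differentiation and MetS components". The Methods paragraph of the Abstract is wider: "logistic regression will examine associations between syndrome differentiation, metabolic parameters, lifestyle factors, and disease progression". Neither place lists a covariate.

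The groups come from a model: "Latent class analysis will be used to identify the TCM syndrome patterns". How participants are assigned to classes, and how assignment error enters later comparisons, is not stated.

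The Study Outcomes section shows what is collected. The secondary outcomes begin with demographic and anthropometric measurements and end with "Framingham Stroke Risk Score (FSRS), retinal imaging, and concurrent medications". Age and use of antihypertensive drugs are among the inputs to that risk score. Strengths and Limitations concedes that "potential confounding factors could affect result interpretation" but gives no analytic remedy.

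**The concern.** A comparison of syndrome groups without covariates answers a descriptive question: how do people with different patterns differ on average? The Discussion asks for more. The Overview speaks of value in predicting outcomes, and Anticipated Principal Findings of prognostic stratification and personalized management. Those claims need syndrome to carry information beyond what age, sex and treatment already give.

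Confounding by age is plausible here for three reasons.

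- Eligibility covers 18 to 75 years.
- Several of the 69 SDQTM items that would define the classes (hearing problems, loss of teeth and hair, poor memory, passing urine at night) can be expected to become more common with age.
- Age is a direct input to the stroke risk score, so any age gap between classes enters that outcome by construction.

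The eligibility criteria also admit people already treated for hyperglycemia or hypertension, so some glucose and blood pressure values are on-treatment values.

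A second, smaller issue concerns the class labels. If each participant is given one latent class and that label is then treated as exact, assignment errors blur the groups.

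**Working it through.** **What each method can do.** The protocol article gives no figure on this point, so the methods are set side by side first.

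| Method named | Data | Takes covariates as named? | Covariates listed |
|---|---|---|---|
| One-way ANOVA, Kruskal-Wallis | quantitative | no | none |
| Chi-square, Fisher exact | categorical | no | none |
| Spearman, Kendall tau-b | continuous, ordinal | no | none |
| Logistic regression | MetS components (Statistical Analysis); also lifestyle factors and disease progression (Abstract) | yes | none |

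On the Statistical Analysis wording, sleep, diet, activity, quality of life, retinal measures and the risk score are left to the first three rows.

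**Inputs to the simulations.** From the protocol article: N = 470 (recruitment target) and two-sided alpha 0.05. Assumed, because the documents give no values: three equal classes, a standardized outcome, the age gap between classes, the age-outcome correlation and the accuracy of class labels. There were 2,000 runs per setting. The Monte Carlo standard error near 5% is sqrt(0.05 × 0.95/2000) = 0.005.

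**(a) Age gap, no true syndrome effect.** Adjacent classes differ in mean age by *a* within-class SD, and age correlates *r* with the outcome within class. The spurious difference between the extreme classes is 2 × *a* × *r* SD: 2 × 0.2 × 0.1 = 0.04 SD at the low end and 2 × 0.5 × 0.3 = 0.30 SD at the high end. If the age SD were 8 years (assumed), the non-zero gaps would be 0.2 × 8 = 1.6 to 0.5 × 8 = 4 years between adjacent classes.

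Share of runs in which unadjusted ANOVA rejects the true null:

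| Age gap *a* | *r* = 0.1 | *r* = 0.2 | *r* = 0.3 |
|---|---|---|---|
| 0 | 4.6% | 4.0% | 4.7% |
| 0.2 | 6.7% | 8.9% | 14.0% |
| 0.3 | 7.1% | 13.8% | 28.1% |
| 0.5 | 12.3% | 33.0% | 65.4% |

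With age in the model, the F test for class rejects in 4.0% to 6.2% of runs across the same twelve settings.

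**(b) Fixed labels with random error.** The true step between adjacent classes is 0.20 SD, so the extreme classes differ by 0.40 SD. A share (1 − *acc*) of labels is wrong at random, split equally between the other two classes and independent of the outcome. The expected difference is 0.40 × [*acc* − (1 − *acc*)/2]. At 80% accuracy this is 0.40 × (0.80 − 0.10) = 0.28 SD.

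| Label accuracy | Expected difference | Power of ANOVA |
|---|---|---|
| 100% | 0.40 SD | 89% |
| 95% | 0.37 SD | 85% |
| 90% | 0.34 SD | 76% |
| 80% | 0.28 SD | 59% |
| 70% | 0.22 SD | 38% |

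With no true difference, the rejection rate stayed between 4.4% and 5.7% at every accuracy. Random label error therefore attenuates and costs power. It does not create false differences.

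**The case against.** The strongest reply has four parts.

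- **Logistic regression is planned, can adjust, and is nowhere said to be unadjusted.** This stands, and a reader who infers that the study has no adjustable analysis goes too far. But the Statistical Analysis section confines that model to MetS components. Even on the Abstract's wider wording, quality of life is not covered. An unseen analysis plan could add covariates to the logistic model, but it could not add them to ANOVA or Kruskal-Wallis. It would have to use other methods there.
- **The stated objective is to characterize syndrome profiles, for which unadjusted comparison is legitimate, and the limitations disclose confounding and disclaim causality.** This stands for description. It does not cover the prognostic and personalized-management claims.
- **One fixed label per participant is not stated.** This stands. It is inferred from the choice of tests that need a group label and from the planned adjusted Rand index between classifications. A reader might infer that the plan treats the class as known, but the text does not say so.
- **The sizes depend on assumptions.** This stands too. No class-specific ages, correlations or accuracies are given, so no single error rate can be assigned to this study.

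**Conclusion.** The point holds as a weakness in the stated methods for association claims. The group-comparison tests fixed in the protocol article cannot adjust, the one model that could is narrow in scope and names no covariate, and relevant variables are collected. Followed as written, the plan could attribute age differences to syndrome, most directly in the stroke risk score.

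A reader might infer that the differences will be confounded. The documents support only that they may be: bias needs both a covariate gap between classes and a link from that covariate to the outcome. Over the assumed settings, false rejection runs from about 4% (no age gap) to about 65% (0.5 SD gap, correlation 0.3), against about 4% to 6% after age adjustment.

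The class-label issue is conditional on fixed labels being used. Its effect under random error is attenuation, for example 0.40 SD to about 0.28 SD at 80% accuracy, with type I error unchanged.

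**What to change.** Keep ANOVA, Kruskal-Wallis, chi-square and Fisher tests as descriptive. For association claims:

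1. Regress each outcome on syndrome class (linear, ordinal or logistic, according to the outcome), adjusted for age and sex. Sex is not listed by name but is implied by the demographic data and the sex-specific waist cut-offs.
2. Add a sensitivity model with concurrent medication classes. Include diabetes duration only if it is recorded: the Discussion expects relationships with it, but it is not among the listed measures.
3. For the stroke risk score, do not adjust for its own inputs, such as age and antihypertensive use. Show the score by class within age strata instead.
4. Carry class uncertainty into these models with a bias-adjusted three-step method (BCH or ML) or by weighting on posterior class probabilities.
5. State one scope for the logistic regression, so that the Abstract and the Statistical Analysis section agree.

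The cost is modest analysis work. Age, demographics and medications are already being collected. Adjusted differences may be smaller than unadjusted ones. More than 450 participants had completed data collection by October 2025, so the change should be fixed before the syndrome comparisons are seen.
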